**Part III: Respondents’ Obstetrics and Gynecologic related factors**

| **Sr. No.** | **Questions** | **Choices of response** | **Skip to** |
| --- | --- | --- | --- |
|  | What was your age when you married for the first time? | --------------- years completed |  |
|  | Did you have a history of pregnancy terminated before seven months? | 1. No 2. Yes |  |
|  | Did you give childbirth after seven months of pregnancy? | 1. No 2. Yes | If no, go to Q312 |
|  | If yes, what was your age at first delivery? | --------------- in years  999……… don’t know |  |
|  | How many children you delivered? | ___________no. of delivery |  |
|  | What was your age at last delivery? | ---------- years |  |
|  | Which mode of delivery have you ever faced?  More than one option is possible | 1. Spontaneous vaginal delivery 2. Cesarean delivery 3. Assisted instrumental delivery |  |
|  | Have you ever experienced labor that lasted more than one day and night (>24hrs)? | 1. No 2. Yes |  |
|  | Have you ever given birth at home (previously)? | 1. No 2. Yes |  |
|  | Where did you deliver your last child? | 1. At home 2. Health facility |  |
|  | When did you start household work after delivery of your last baby? | ----------- days  ……….. weeks after delivery |  |
|  | Do you have a history of pelvic surgery (episiotomy, hysterectomy, trauma, tumor removal) | 1. No 2. Yes |  |
|  | Is your menstrual cycle stopped permanently (more than 3 cycles)? Without contraceptive use? | 1. No 2. Yes |  |
|  | If yes for Q-313, for how long? | ------------- |  |

| **Part-IV: Study participants wealth Index**  Ask (and observe when possible) the following questions one at a time and write the response on the space provided or encircle the appropriate response from the options listed. | | | | | |
| --- | --- | --- | --- | --- | --- |
|  | What is the main source of drinking water for members of your household? | Piped water:   - 1. Piped into dwelling   2. Piped to yard/plot   3. Public tab/standpipe   4. Borehole | | |  |
|  |  | Dug well:   1. Protected well 2. Unprotected well | | |  |
|  |  | Water from spring:   1. Protected spring 2. Unprotected spring | | |  |
|  |  | Surface water:   - - - 1. River/lake/pond/stream/dam | | |  |
|  | What is the main source of water used by your household for other purposes such as cooking and handwashing? | Piped water:   1. Piped into dwelling 2. Piped to yard/plot 3. Public tab/standpipe 4. Borehole | | |  |
|  |  | Dug well:   1. Protected well 2. Unprotected well | | |  |
|  |  | Water from spring:   1. Protected spring 2. Unprotected spring | | |  |
|  |  | Surface water:   1. River/lake/pond/stream/dam | | |  |
|  | Where is that water source located? | 1. In own dwelling  2. In own yard/plot  3. Elsewhere | | |  |
|  | How long does it take to go there, get water, and come back? | 1. Minutes __________ 2. Don’t know | | |  |
|  | In the past two weeks, was the water from this source not available for at least one full day? | 1. N0 2. Yes 3. Don’t know | | |  |
|  | Do you do anything to the water to make it safer to drink? | 1. No ------------------------------------- 2. Yes | | | 4.8 |
|  | What do you usually do to make the water safer to Drink?  Record all mentioned | 1. Boil 2. Add bleach/chlorine 3. Strain through a cloth 4. Use water filter (Sand/composite/etc.) 5. Solar disinfection 6. Let it stand and settle | | |  |
|  | What kind of toilet facility do members of your household usually use? | **FLUSH OR POUR-FLUSH TOILET**   1. Flush to a piped sewer system 2. Flush to septic tank 3. flush to a pit latrine 4. Flush to somewhere else 5. Flush, don't know where   **PIT LATRINE**   1. Ventilated improved pit latrine 2. Pit latrine with slab 3. Pit latrine without slab/open pit 4. composting toilet 5. bucket toilet 6. Hanging toilet/hanging latrine 7. No facility/bush/field | | |  |
|  | Do you share this toilet facility with other households? | 1. No 2. Yes | | |  |
|  | Including your own household, how many households use this toilet facility? | 1. Less than 10 2. 10 or more 3. Don't know | | |  |
|  | Where is this toilet facility located? | 1. In own dwelling 2. In own yard/plot 3. Elsewhere | | |  |
|  | What type of fuel does your household mainly use for cooking? | 1. Electricity 2. Liquid petroleum gas 3. Natural gas 4. Biogas 5. Kerosene 6. Charcoal 7. Wood 8. Straw/grass 9. Agricultural crop 10. Animal dung 11. No food cooked in house | | |  |
|  | Is the cooking usually done in the house, in a separate building, or outdoors? | 1. In the house 2. In separate building 3. Outdoors 4. Other | | |  |
|  | Do you have a separate room which is used as a kitchen? | 1. Yes 2. No | | |  |
|  | Who is the owner of the house? | 1. Me 2. Rental 3. Family 4. Relative 5. Others (specify)_________________ | | |  |
|  | How many rooms in this household are used for sleeping? | --------Rooms | | |  |
|  | Main material of the roof of the house? | 1. Natural roofing (no roof, mud, and sod) 2. Rudimentary roofing (rustic mat/plastic sheet, reed/bamboo, wood planks, and cardboard) 3. Finished roofing (metal/corrugated iron, wood, calamine/cement, ceramic tiles, roofing shingles) | | |  |
|  | Main material of the floor of the house? | 1. Natural floor (Earth/sand, dung) 2. Rudimentary floor (wood planks, and palm/bamboo) 3. Finished floor (parquet or polished wood, vinyl or asphalt strips/ plastic tiles, cement, ceramic tiles, carpet) | | |  |
|  | Does this household own any livestock, herds, other farm animals, or poultry? | 1. No 2. Yes | | |  |
| - - 1. 4 | How many of the following animals does this household own?  IF NONE, RECORD '00'.  IF 95 OR MORE, RECORD '95'.  IF UNKNOWN, RECORD '98'. | 1. Cows bulls_______________ 2. Other cattle______________ 3. Horses/Donkeys/Mules ____ 4. Camels________ 5. Goats _________ 6. Sheep _________ 7. Chickens/poultry ______ 8. Beehives ___________ | | |  |
| - - 1. 421 | Do you have separate rooms for cattle? | 1. Yes 2. No | | |  |
| - - 1. 422 | Does any member of this household own any agricultural land? | 1. No --------------------------------------- 2. Yes | | | 4.24 |
| - - 1. 423 | How many hectares of agricultural land do members of this household own? | ___________hectares | | |  |
| - - 1. 424 | Which of the following does your household have? (Multiple answers possible) |  | Yes (1) | No (0) |  |
|  |  | 1. Electricity---------- 2. Radio--------------- 3. Television --------- 4. Non-mobile telephone---------- 5. Computer ---------- 6. Refrigerator ------- 7. Table---------------- 8. Chair --------------- 9. Bed with spring matters------------ 10. Electric mitad ----- 11. Kerosene lamp/pressure------ 12. Lamp--------------- |  |  |  |
|  | Does any member of this household own: |  | Yes (1) | No(0) |  |
|  |  | 1. Watch -------------- 2. Mobile phone------ 3. Bicycle------------- 4. Motorcycle/scooter- 5. Animal-drawn cart- 6. Car/truck ------------ 7. Boat with motor----- 8. Baggage ------------ |  |  |  |
| - - 1. 426 | Does any member of this household have a bank account? | 1. No 2. Yes | | |  |
| - - 1. 427 | Does any member of this household have a micro finance account? | 1. No 2. Yes | | |  |
|  | How often does anyone smoke inside your house?  Would you say daily, weekly, monthly, less often than once a month, or never? | 1. Daily 2. Weekly 3. Monthly 4. Less often than once a month 5. Never | | |  |

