## Study Population

All women who have given birth (at least once) or ≥ 18 years old, and permanent residents (≥ 6months) of the Health and Demographic Survey Site of Hawassa University will be included in this study.

**Inclusion Criteria:** Women whose household information is found in the Health and Demographic Survey of Hawassa University and who have given birth or ≥ 18 years old will be included.

**Exclusion criteria:** Women who are pregnant (confirmed or suspected), in the postpartum period (six weeks), never practiced sexual intercourse, or severely sick during the data collection period will be excluded.

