## Study Variables

The outcome variable of this study is pelvic organ prolapse. The independent variables include: Age in years, mode of delivery, number of childbirth, level of education, body mass index, history of pelvic surgery, trauma, marital status, occupation, heavy lifting, smoking, age at first marriage, age at first delivery, place of delivery, history of instrumental delivery, history of a length of labor more than 24hrs (one day), medical conditions (chronic cough, Diabetes mellitus, hypertension), family history of POP, ethnicity, duration menopause.

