## Variables

The outcome variable of this study is a change in Pelvic Organ Prolapse Symptom as measured by POP-SS and the intervention is Pelvic Muscle Training. Covariates include degree of POP, the severity of POP-SS, adherence to Pelvic Floor Muscle Training protocol, maternal age, location of POP, history of pelvic surgery, number of childbirth, level of education, body mass index, trauma, marital status, occupation, age at first marriage, age at first delivery, place of delivery, history of prolonged labor, medical conditions (chronic cough, diabetes mellitus), family history of POP, mode of delivery, duration since last menstrual period.

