**Gaamo III: Amuwu Ilaranna Otoottote Fayyimma Ledo Xaadinohunni Xa’minanni Borri-xa’mo**

| **A.k.** | **Xa’muuwa** | **Dawaaro** | **Sa’i** |
| --- | --- | --- | --- |
|  | Umikki yannara mine assi’roottahu meyikki dirikkiraati? | --------------- dirooti |  |
|  | Lamala agana ikkinokkiha, umo ka’e egennootanni? | 1. Dee’ni 2. Ee |  |
|  | Lamalu aganni gedensanni ilite eggenotanni? | 1. Dee’ni ___________ 2. Ee | sa’i 312 |
|  | Xa’mo303, ee. ikkiro umo ilitta woyite meyikki deerikkiraati? | --------------- dirooti  999……… diafoomma |  |
|  | Me’’e qaaqquulle ilitta? | ___________hige iloomma |  |
|  | Gedeniidi qaaqqo ilitta yannara meyikki dirikkiraati? | ---------- dirooti |  |
|  | Hitoonni ilte egennootta?  (Mittu aleenni doora dandiinanni ) | 1. Qarru noyikkiha iloomma 2. Godowa dadhatenni 3. Udiinnichu kaa’lonni iloomma |  |
|  | Mitto barra sae/(24) saate sae gamaa’mite egennoottanni? | 1. Dee’ni 2. Ee |  |
|  | Sa’u yanna giddo mine ilte egennootanni? | 1. Dee’ni 2. Ee |  |
|  | Gedensiidikki qaaqqo hiikko ilootta? | 1. Mine 2. fayyimmate uurinshara. |  |
|  | Gedensiidi qaaqqo ilittahu gedensaanni, meyikkita mini looso loosa hanafootta? | ----------- barrinni  ……….. lamalate gedensaanni |  |
|  | Godowa dadhite egennootanni? (qaaqqu fula giweennae shiima darga darroonnie, otoottote darroonnie ,danotenni darroonnie, godowi giddo darshinore holaara darroonnie) | 1. Dee’ni 2. Ee |  |
|  | Aganu mundeekki horontanni uurritinoni? (sasu aganni aleenni)? Maatete damboowishsha horoonsi’rittakkinni | 1. Dee’ni 2. Ee |  |
|  | Xa’mo 313, ‘’ee’’ yiittaro, mageeshshi yanna? | ------------- |  |

| **Gaamo -IV: Jajju woy Jirote Amadooshshe**  Konni worooninoo xa’mubba xa’mateni (dandaamiro la’atenni) gara ikkitino dawaro dooni. | | | | | |
| --- | --- | --- | --- | --- | --- |
|  | Maatekki agganno waa afidhannohu hiikkiinniiti? | Baambu waa :   1. Mini giddo baambu waa 2. Hoowete afamanno baambu waa 3. Dagoomu tuqi horoonsi’ranno baambu waa 4. Umme fushshinoonni waa | |  | |
|  |  | Agarooshshe:   1. Garunni agaraminoha 2. Garunni agaraminokkiha | |  | |
|  |  | Buete waa:   1. Garunni agarroonnita 2. Garunni agarroonnikkita | |  | |
|  |  | Daadanno Waa:  1.Lagu/garbu/kofaminoha/xashshuwa/ waa | |  | |
|  | Maatekki sagale loosi’ratenna anga hayishshi’rate horoonsidhanno waa maminni afidhanno? | Baambu waa:   1. Mini giddo baambu waa 2. Hoowete afamanno baambu waa 3. Dagoomu tuqi horoonsi’ranno baambu waa 4. Umme fushshinoonni waa | |  | |

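### Paper II: the menopause item counts more than three missed cycles as permanently stopped menses, so breastfeeding women without periods can be recorded as menopausal

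*Protocol*

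**What the plan says.** In the English questionnaire (Annex II, Part III) menopausal status comes from one item, "Is your menstrual cycle stopped permanently (more than 3 cycles)? Without contraceptive use", followed by "If yes for Q-313, for how long". The follow-up has no unit and no minimum. The Sidaamu Afoo version in Annex III, "Aganu mundeekki horontanni uurritinoni? (sasu aganni aleenni", appears to carry the same threshold of more than three (months) and adds no breastfeeding condition.

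The Study Population section of Paper II takes in "All women who have given birth (at least once) or ≥ 18 years old", so women of childbearing age are included. Among its exclusions are "Women who are pregnant (confirmed or suspected), in the postpartum period (six weeks), never practiced sexual intercourse". Breastfeeding is not an exclusion, and no questionnaire item asks about it. The nearest information on a recent birth is "What was your age at last delivery", recorded in years.

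Among the Paper II independent variables is "family history of POP, ethnicity, duration menopause". The Data Source and Measurement section of Paper II defines body mass index, heavy lifting and pelvic surgery, but not menopause. The trial's covariate list (Paper III, Variables) ends with "family history of POP, mode of delivery, duration since last menstrual period"; the Paper IV list has no such variable.

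**The concern.** The item asks about permanence but attaches a rule that a temporary absence of periods can meet. A woman five months after birth, breastfeeding and not yet menstruating, is eligible, uses no contraception, and has missed more than three cycles. Nothing on the form separates her from a woman who has reached menopause.

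The literature review presents menopause as acting independently of age and parity, and says that local evidence on its link with prolapse is inadequate. Identifying risk factors is the second objective of Paper II. Pooling young, recently delivered women with menopausal women blurs an exposure that the protocol itself calls under-studied. The fault lies in the data-collection form, so an analysis plan could repair it only in part: breastfeeding status is never recorded.

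**Working it through.** **Can such a woman be coded yes?** She passes eligibility once six weeks have gone by since birth. Three months after birth she meets the bracketed rule on time since birth alone; if the months of pregnancy are counted, she meets it as soon as she is eligible. Contraception, the one named exception, does not apply to her. The item therefore allows a yes, though it does not force one.

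**Size for a yes/no exposure.** The protocol has no figure to reproduce and gives neither shares nor effect sizes, so all inputs except the sample size are assumptions:
- N = 816 (Paper II, Sampling Techniques), weights ignored
- truly menopausal share m = 0.25
- share q of the remaining women who are wrongly coded yes = 0.05, 0.10 or 0.20
- prolapse risk 0.50 in women who are not menopausal, including those wrongly coded
- true odds ratio 2.0, so risk in menopausal women = 2/3

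False share of all yes answers: f = (1 − m)q / [(1 − m)q + m].
Risk among all yes answers: r = (1 − f)(2/3) + f(0.50).
The odds in the unexposed are 1, so the observed odds ratio = r/(1 − r).

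| q | Wrongly coded, of 816 | f | r | Observed odds ratio |
|---|---|---|---|---|
| 0.05 | 0.75 × 0.05 × 816 = 31 | 0.0375/0.2875 = 13% | 0.645 | 1.82 |
| 0.10 | 0.75 × 0.10 × 816 = 61 | 0.075/0.325 = 23% | 0.628 | 1.69 |
| 0.20 | 0.75 × 0.20 × 816 = 122 | 0.15/0.40 = 38% | 0.604 | 1.53 |

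**Wider assumptions.** Here m is 15% to 25%, the wrongly coded women are 5% to 20% of *all* women, and the unexposed risk is 30% to 50%. A true odds ratio of 2 is then seen as 1.33 to 1.79, and a true 3 as 1.55 to 2.52.

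**If breastfeeding women carry extra risk.** With 10% of all women wrongly coded and their own odds ratio at 1.5, a true 2 is seen as 1.78 to 1.84. The dilution is smaller.

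**Short-duration category.** Suppose true durations are spread evenly over 0.5 to 20 years and breastfeeding durations lie below 2 years. Truly menopausal women in the group of two years or less are then m × 1.5/19.5 of the sample. With m = 0.25 and 5% wrongly coded, breastfeeding women make up 0.05/(0.05 + 0.0192) = 72% of that group. With m = 0.15 and 20% wrongly coded they make up 0.20/(0.20 + 0.0115) = 95%.

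**Linear duration term.** Under the same duration assumptions, with menstruating women at zero, a simulated logistic model gave a fitted slope of 0.99 to 1.02 times the true one. Breastfeeding women sit close to zero on the duration scale and hardly move the line.

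**Which form will be used?** The Data Management and Analysis section of Paper II screens for confounding with stratified Mantel-Haenszel estimates, which need categories. It fixes no cut-points for menopause and does not say how duration enters the logistic model.

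**The case against.** The strongest reply is that the item does ask about permanence. A young mother who expects her periods to return can truthfully answer no, and the Sidaamu Afoo wording uses *horontanni*, the same word that its symptom scale uses for never. This stands in part. A reader might infer that every such woman answers yes, and the documents do not show that, so the assumed shares lean high. But a question that carries both permanence and a three-cycle rule leaves the choice to the respondent or interviewer.

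A second reply is that the listed variable is a duration, for which the odds ratios in the table do not apply. This is right for a single linear term, and the claim is limited accordingly.

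A third is that recorded duration, current age and age at last delivery allow recoding, and that tools other than the symptom score will be pretested on 41 women so that unclear items can be changed. Both help. The recode is only partial, and the pretest is a convenient moment for the rewording.

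Two stronger readings are tempting and should not be made:
- **That the trial covariate is wrong in the same way.** It is named as time since the last menstrual period, and for a breastfeeding woman that value is literally correct. It is absent from the Paper IV list and does not enter the between-arm t-test of mean change.
- **That recent childbirth, as a risk factor in its own right, is mixed into the variable.** The literature review names vaginal delivery, parity, forceps, prolonged labour and age at first delivery, but not time since birth. Raised risk in these women would also reduce the dilution, not add to it.

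**Conclusion.** The point holds as a measurement weakness in Paper II. By its own bracketed rule, the item can record breastfeeding women without periods as menopausal, and nothing in the eligibility criteria, the form or the variable definitions prevents it. The dilution matters if menopause is analysed as yes/no or in short-duration categories, as the Mantel-Haenszel step implies: a true odds ratio of 2.0 would be seen as about 1.5 to 1.8. That range rests on assumed shares (25% truly menopausal, 5% to 20% of the others answering yes) and on baseline risk in the misclassified women. Fewer such answers, or raised risk in these women, would make the dilution smaller. For a purely linear duration term the effect is negligible. The prevalence estimate is not touched, and the randomised comparison is not materially affected. It is worth correcting because the change is small and breastfeeding status cannot be recovered directly once data are collected.

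**What to change.** Reword the item in Annexes II and III to ask whether periods have stopped for 12 months or more when the woman is not pregnant, breastfeeding or using contraception. Keep the duration follow-up and print its unit.

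If forms are already printed, instruct interviewers to write the unit and add a recode rule. Treat a yes as not menopausal when the stated duration is under 12 months, and flag for review any yes where current age is within about two years of age at last delivery. This is a partial remedy. Ages are in whole years, so a recorded gap of one year can stand for anything from just above zero to just under two years, and an entry without a unit cannot be recoded safely.

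The cost is one reworded item and one unit in each language, or one recode rule. The downside is that women in the first year after their final period are counted as not yet menopausal.

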**PART-V: POP-SS**

**Direction**

The following seven questionnaires are standard tools used to measure prolapse symptoms. Each item/question has 0 to 4 possible response scales. Inform the participant how to give a rate for each item based on how often she felt the prolapse symptom in the last four weeks (Put ‘X’ in the right box under each response scale).

Dear participant, please tell me how often did you feel the following POP symptoms in the last four weeks? (Please give the rating scale as follows: 0= never felt symptom in the last four weeks, 1= occasionally, 2= sometimes, 3= most of the time and 4= all of the time)

| **S.no** | **POP-Symptoms** | **0**  never felt symptom in the last four weeks | **1**  occasionally | **2**  sometimes | | **3**  most of the time | **4**  all of the time |
| --- | --- | --- | --- | --- | --- | --- | --- |
|  | A feeling of something coming down from or in your vagina? |  |  |  | |  |  |
|  | An uncomfortable feeling or pain in your vagina which is worse when standing? |  |  |  | |  |  |
|  | A heaviness or dragging feeling in your lower abdomen/tummy? |  |  |  | |  |  |
|  | A heaviness or dragging feeling in your lower back? |  |  |  | |  |  |
|  | A need to strain (push) to empty your bladder? |  |  |  | |  |  |
|  | A feeling that your bladder has not emptied completely? |  |  |  | |  |  |
|  | A feeling that your bowel has not emptied completely? |  |  |  | |  |  |
|  | Which of the symptoms above (questions 1–7) causes you most bother? | ……………. | | | | | |
|  | For how long have you felt one of the most chronic symptoms? | ……… | | | | | |
| **Patient Global Impression of Change questionnaire**  Ask the following questions only at end-line assessment (after intervention). Both the control and interventional group participants will be asked at the end of six months. | | | | | | | |
|  | How do you Perceive the change in prolapse since the start of the intervention? | | | | 1= Very much improved  2= Much improved  3= Minimally improved  4 = No change  5= Minimally worse  6= Much worse  7= Very much worse | | |

**Part-VI: Pelvic Floor Disability Index (PFDI-20)**

**Instructions:** Please answer all of the questions in the following survey. These questions will ask you if you have certain bowel, bladder, or pelvic symptoms and, if you do, **how much they bother you**. While answering these questions, please consider your symptoms over the last 3 months.

**Pelvic Organ prolapse Distress Inventory 6 (POPDI-6)**

| ***S.No*** | ***Do You…*** | **NO** | **Yes** | | | |
| --- | --- | --- | --- | --- | --- | --- |
|  |  | 0  **not present** | 1  **not at all** | 2 **somewhat** | 3 **moderately** | 4 **quite a bit** |
|  | Usually experience pressure in the lower abdomen? |  |  |  |  |  |
|  | Usually experience heaviness or dullness in the pelvic area? |  |  |  |  |  |
|  | Usually have a bulge or something falling out that you can see or feel in your vaginal area? |  |  |  |  |  |
|  | Ever have to push on the vagina or around the rectum to have or complete a bowel movement? |  |  |  |  |  |
|  | Usually experience a feeling of incomplete bladder emptying? |  |  |  |  |  |
|  | Ever have to push up on a bulge in the vaginal area with your fingers to start or complete urination? |  |  |  |  |  |

